**Figure 2 figure2:**
[figure not shown]
The steps of the content validity of the CHILD-MHL scale. MHL: mental health literacy.

### Refinement: Viability Evaluation of the Intervention and Scale Validation

#### The Viability Evaluation of the Intervention

Conducting a viability evaluation refers to collecting stakeholders’ views and experiences regarding whether the intervention is acceptable, practical, affordable, suitable, integrable, helpful, and sustainable in real-life conditions. For this purpose, a pilot test will be conducted in 4 randomly selected classes, representing various settings (1 REP, 1 rural, 1 urban, and 1 private), within the participating department, involving about 130 children. This number is defined by convenience in an attempt to consider social and territorial disparities.

The principal investigator and the research assistant will monitor how the intervention is carried out and identify the barriers and levers for its implementation. About 15 people among teachers, school psychologists, nurses, school directors, parents, and pupils (purposive sample) will be interviewed for feedback. In particular, the directors of the school will be interviewed to comment on the intervention, its advantages and disadvantages, and whether they think that it can be routinely conducted in their schools. Satisfaction questionnaires will be administered to all participants in the viability study. Data from observations, semistructured interviews, and questionnaires will be analyzed through the mixed methods design.

The intervention (contents, form, and language elements) will also be adapted considering the socioeconomic inequalities. For instance, some tools could be canceled or repeated. Teachers from REP areas will receive extra incentives (salary or learning credits) subject to authorization by the academy.

The viability evaluation conditions will mirror the real implementation of the intervention in the cRCT, with the objective of identifying and addressing potential difficulties and inaccuracies on a tool-by-tool basis.

At this stage, we will define and test the process of recruitment: how to inform schools and teachers (eg, through the academy with flyers, mailing, and videos) and how to obtain the consent of parents (eg, an explanation of the intervention through a detailed booklet, access to all tools for checking their contents). Parents will be informed through school mobile apps, contact book (carnet de liaison), and school meetings. All information will help assess the intervention’s replicability. The viability evaluation will study whether and how teachers can conduct the program autonomously.

This pilot phase is also useful for the implementation of the cRCT because we will record all difficulties encountered while conducting the intervention (eg, access to schools and teachers’ availability).

#### Analysis of Current Policies for Promoting Mental Health in Schools

To verify whether the effectiveness of the intervention is driven by a favorable political environment, we will identify and analyze policies and road maps promoting school-based mental health programs at the micro (department) and macro (France) levels. This mapping will involve approximately 5 semistructured interviews with rectors from various regions and departments, and ideally, some members of the Ministry of National Education and Youth’s cabinet. All collected materials will be synthesized in a narrative review and used to write a policy brief aimed at explaining the need for including MHL interventions in schools in addition to existing mental health–related programs. If the CHILD-MHL intervention effectively increases children’s MHL, we will investigate if this success is emphasized by the local political environment. This might reinforce the need for decision makers to include MHL in all educational policies.

#### Validation of the CHILD-MHL Scale

We will use a specific procedure called COSMIN (Consensus-Based Standards for the Selection of Health Measurement Instruments) [67] for scale validation. The questionnaire including the scale and other variables of interest will be initially administered to children from 10 classes from different schools (ie, around 250 children). Half of these classes are those of the viability evaluation. The sample size of 250 respondents is acceptable, considering feasibility and following the rule of thumb of 10 respondents per item [68]. Besides, feasibility must be considered for data collection. Data will be recorded on a tablet for each child consecutively, with supervision provided by the principal investigator and the research assistant. The research assistant will be the only person in possession of a document containing the child’s name and the corresponding code, allowing for matching the questionnaire administrations. The data from the initial administration will be analyzed to assess the scale’s dimensionality and whether the 60 items adequately cover the 6 dimensions of the Child-Focused MHL model. Exploratory and confirmatory factor analyses will be performed. At this stage, it will be possible for the consortium to add or remove items to cover the 6 dimensions.

After 3 months, the questionnaire with the scale, which might have been modified, will be readministered for the second time to all 250 children from the 10 classes during the week preceding the start of the viability evaluation intervention. This second data collection is essential if the scale has been modified and is highly recommended to refine the scale dimensions. Using this large data set, analyses will be performed to reduce the number of items by employing the Classical Test Theory and the Item Response Theory [69]. Exploratory and confirmatory factor analyses will be performed again to assess the dimensionality and structural validity of the scale. For the convergent and discriminant validity of the scale, the questionnaire will include other variables, including, sex, age, or emotional status measured by the KIDSCREEN-10 [70]. We will check for variations in the scores of scale dimensions among different groups.

Children from the 5 classes of the viability evaluation intervention will complete the questionnaire for the third time after a 3-month interval (ie, the maximum time of the intervention). Data collected from these classes will be used to assess the sensitivity to change or responsiveness of the scale. If the score changes after the intervention, it indicates that the scale can measure the effect of the intervention on children’s MHL. In this case, the items are expected to be “actionable,” meaning that interventions can influence them and lead to changes in the results.

Finally, children not receiving the intervention will answer the questionnaire for the third time after a month. Data will be used to assess the test-retest reliability, determining whether answers remain consistent between administrations and if the items are stable over time. Figure 3 illustrates the phases of the data collection and data analyses for scale validation.

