#### Preparation of the CHILD-MHL Scale

A total of 95 items have already been identified by the founders of the Child-Focused MHL model [27] through a rigorous Delphi study with more than 30 experts. The principal investigator and the research assistant will add items from other MHL scales for adolescents and adults [37,42,64] (inventory of MHL scales) to have a comprehensive list of items necessary to use a reflective model in the definition of the MHL construct. All items will be translated into French and categorized according to the 6 dimensions of the Child-Focused MHL model. We expect a maximum of 150 items.

The consortium will convene online, exchange emails, and use shared documents to streamline the number of items to 60 (ie, 10 per dimension), which corresponds to the first draft of the scale. This number is planned with the objective of limiting the final scale to a maximum of 24-30 items for ease of administration, especially for children who may encounter difficulties due to factors such as limited attention span or the complexity of the tasks. Literature suggests that a preliminary scale must contain 2-3 times the number of items of the final scale and that there must be at least three or four items per dimension [65].

The items will be discussed with a group of 5 parents and 5 teachers to adapt them to children (language and contents). A group of 5 children, who will be recruited from a recreation center (*centre de loisirs*) in a randomly selected area, will then codraw with 1 designer/artist, as a craft activity, the items to obtain a more understandable digital visual scale during a 2-hour workshop. Finally, this scale will be administered to 25 or 30 children from a class randomly selected by a French academy. Each child will be interviewed to assess whether the items are understandable and clear.

In parallel, the same scale will be sent to around 30 experts (eg, psychologists, teachers, health promotion professionals, researchers, and statisticians) who will have to rate each item and complete a checklist measuring the practicality, acceptability, clarity, and appropriateness of the scale.

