We have also compiled the initial list of items (n=56) for the scale. These 56 items were listed by 2 public health researchers, and revised by 11 experts in the field of child health, including child psychiatrists and developmental psychologists. These items will then undergo further review by a panel of at least 30 experts, including psychologists, educators, and public health researchers. Following this selection process, 1 artist will collaborate with children to illustrate the items. Subsequently, the scale will be administered to several hundred children to collect data for psychometric analyses.

Finally, we compiled a report listing the existing education policies for children’s mental health in France.

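### The 250 children for scale validation are said to follow a rule of 10 respondents per item, but the 60-item draft they complete gives about 4 per item

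*Protocol article*

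**What the plan says.** All references are to the protocol article; no separate statistical analysis plan is shown.

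- **Draft length.** Preparation of the CHILD-MHL Scale has the consortium "streamline the number of items to 60 (ie, 10 per dimension), which corresponds to the first draft of the scale".
- **Intended final length.** The same section gives the aim of "limiting the final scale to a maximum of 24-30 items for ease of administration".
- **Sample.** Under Validation of the CHILD-MHL Scale, the questionnaire is "initially administered to children from 10 classes from different schools (ie, around 250 children".
- **Justification.** The same paragraph says: "The sample size of 250 respondents is acceptable, considering feasibility and following the rule of thumb of 10 respondents per item".
- **Use of the first administration.** Exploratory and confirmatory factor analyses will assess dimensionality and "whether the 60 items adequately cover the 6 dimensions of the Child-Focused MHL model". The consortium may then add or remove items.
- **Second administration.** Three months later the scale, possibly modified, goes back to the same 250 children. Item reduction by Classical Test Theory and Item Response Theory takes place at this stage, and the factor analyses are repeated.
- **Other figures.** Results reports the list compiled so far: "We have also compiled the initial list of items (n=56) for the scale". The Abstract gives 300 children, not 250, for the validation sample.

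**The concern.** The sentence gives a sample size and a rule that it is said to follow. The rule needs an item count, and the only one given in that paragraph is 60. At 10 respondents per item, 60 items and 250 children do not go together.

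The 250 are offered as support for the first look at dimensionality, after which the consortium may change the item set. The scores of the resulting scale are the primary end point of the cluster trial, so readers will rely on what the article says about how the scale was built. Apart from feasibility, the rule is the only ground given for the number. As worded, the sentence tells readers that these analyses meet a standard which they miss by more than half.

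**Working it through.** **Inputs**

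- Rule: 10 respondents per item (Validation of the CHILD-MHL Scale).
- Respondents: 250 (same section); 300 in the Abstract.
- Items: 60 in the draft (Preparation and Validation sections); 56 compiled so far (Results); at most 24–30 in the final scale (Preparation section).

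**Formulas**

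- Respondents implied by the rule = 10 × items.
- Respondents per item = respondents / items.
- Shortfall = 1 − respondents / (10 × items).

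**Step 1. Try to reproduce 250 from the stated draft.** 10 × 60 = 600, so the plan's figure is not reproduced. 250 / 60 = 4.17 per item, and the shortfall is 1 − 250/600 = 58%.

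**Step 2. Use the 56-item list instead.** 10 × 56 = 560. 250 / 56 = 4.46 per item, and the shortfall is 1 − 250/560 = 55%.

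**Step 3. Find the item count at which 250 does meet the rule.** 250 / 10 = 25 items. Against the planned final length:

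| Items | Rule implies | 250 gives per item | Rule met by 250? |
|---|---|---|---|
| 24 | 240 | 10.4 | yes |
| 25 | 250 | 10.0 | yes |
| 30 | 300 | 8.3 | no |
| 56 | 560 | 4.5 | no |
| 60 | 600 | 4.2 | no |

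**Step 4. Test other figures that might rescue the statement.**

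- The Abstract's 300 children: 300 / 60 = 5.0 per item, half of what the rule asks; 300 / 56 = 5.4.
- Both administrations pooled: 2 × 250 = 500 records, and 500 / 60 = 8.3 (500 / 56 = 8.9). This is still below 10, and the records come from the same 250 children, so they are not 500 respondents.

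No pairing of a stated draft length (60 or 56) with a stated sample size (250 or 300) meets the rule.

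**The case against.** **The rule may refer to the final scale.** Ten per item for 24–30 items gives 240–300. The 250 lies in that range, and the Abstract's 300 is exactly 10 × 30. An unstated item count may therefore explain the figure better than a slip of arithmetic. That stands as a plausible origin. It does not rescue the sentence: the text does not say it, it works only up to 25 items, and the 60-item factor analyses are run before any short scale exists.

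**Feasibility is stated as well.** This is true, and the paragraph repeats it. Feasibility can justify 250, but it cannot make 250 follow a rule that it misses. The sentence claims both.

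**A reader might infer that the item reduction itself rests on 60 items at 4.2 respondents each.** The document does not support this. Reduction comes after the second administration, on a scale that may have been modified. Items may have been removed or added by then, so the ratio at that step is unknown. The 4.2 is established for the first administration only.

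**A reader might also infer that the loadings will be unstable and the wrong items kept.** This is not shown. Stability depends on communalities and on the number of items per factor, and the article gives no communalities. Missing a rule of thumb is not evidence of instability. The expert ratings, the interviews with children, and the responsiveness and test-retest work are further checks that do not depend on this ratio.

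**Conclusion.** The statement is wrong as written. For the administration it is meant to support, 250 children give about 4.2 respondents per item with 60 items (4.5 with 56), where the cited rule implies 600 (560). The rule is met only for a scale of at most 25 items, so it fails at the upper end of the planned final length too.

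The conclusion assumes that the rule applies to the items administered and analysed, which is how the paragraph reads. If the final scale was meant, the statement holds for 24 or 25 items and fails from 26 to 30.

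Two stronger readings should be resisted. The figure of 600 is what the article's own rule implies, not proof that 600 children are needed or that 250 are too few. And the shortfall concerns scale validation; it does not bear on the power of the cluster trial. This is an inaccurate justification that should be corrected, but it is not a defect that has been shown to damage the trial, and its priority is moderate.

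**What to change.** Restate the justification in the Validation section. Suggested wording: *250 children, chosen for feasibility, give about 4 respondents per item for the 60-item draft; the 10-per-item rule is met only for a scale of at most 25 items.* Alternatively, drop the rule and rest the number on feasibility alone. If the item count at the first administration turns out to be 56, the ratio becomes about 4.5.

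Also describe the factor analyses of the first administration as provisional where they lead to items being added or removed. They are already due to be repeated after the second administration.

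The cost is wording only: no more children and no change in the order of analyses. Two larger changes may suggest themselves but are not called for. Analysing each dimension separately would presume the six-dimension structure that the first administration is meant to test. Capping the final scale at 25 items would leave the shortfall for the draft where it is.

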### Assessment: cRCT and Semistructured Interviews

#### Implementing the cRCT

We will conduct the cRCT in a minimum of 16 new classes, representing all typologies under the study, from different schools: 4 REP, 4 rural, 4 urban, and 4 private ones (quota sampling). Feasibility will be a major criterion for participant inclusion. Therefore, a minimum of 400 children will be involved in this small-scale cRCT, which is a substantial sample size, as the literature suggests a minimum of 300 participants is sufficient for a cRCT in children [71]. Furthermore, a limited number of participants will allow us to explore in depth the mechanisms influencing the effectiveness of the intervention by analyzing results for each class.

Classes will be randomly assigned to either the intervention group or the control group (on a waiting list without engaging in any activities). Randomization will involve creating matched pairs based on class types, such as pairing 1 urban school class with the intervention and 1 urban school class without the intervention. The CHILD-MHL scale will be administered 1 week before and 2 weeks after the intervention in all classes. We will collect covariates related to children and their environment, including sex, age, school characteristics (geographical and socioeconomic area, population density), parental background (at least one parent not being French, divorced/separated parents), family size (number of siblings), and self-perceived health and emotional status measured by the KIDSCREEN-10 [70]. If possible, with parental consent, teachers will be asked to report whether there is at least one child with a diagnosed mental health problem in the class and provide information on the parents’ socioeconomic situation. Macro-level data will be also included in the analyses (eg, precariousness indexes). The data from the second administration may offer insights into the intervention’s potential impact on children’s well-being and help-seeking actions. Furthermore, participants who received the intervention will respond to closed-ended questions regarding their intention to help someone with a problem, seek help, and their ability to apply strategies for feeling better and recognizing signs of personal distress. The statistical analysis plan will encompass mixed linear models, multilevel models, descriptive statistics, and random effects, with an intention-to-treat primary analysis.

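### The final CHILD-MHL items are selected and confirmed in the same 250 children; the cRCT baseline could test them in at least 400 new ones

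*Protocol article*

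**What the plan says.** All of this is in the protocol article.

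- **First administration** (Validation of the CHILD-MHL Scale). The questionnaire is "initially administered to children from 10 classes from different schools (ie, around 250 children". On these data, "Exploratory and confirmatory factor analyses will be performed. At this stage, it will be possible for the consortium to add or remove items".
- **Second administration** (same section). Three months later the questionnaire, possibly modified, "will be readministered for the second time to all 250 children from the 10 classes". The next step is item reduction by Classical Test Theory and Item Response Theory: "Using this large data set, analyses will be performed to reduce the number of items". Then: "Exploratory and confirmatory factor analyses will be performed again to assess the dimensionality and structural validity of the scale".
- **Third administration** (same section). Subsets of the same children take part. For the classes receiving the intervention, "Data collected from these classes will be used to assess the sensitivity to change or responsiveness of the scale". For the others, "Data will be used to assess the test-retest reliability".
- **Size of the cut** (Preparation of the CHILD-MHL Scale). The draft has 60 items, 10 per dimension, and the final scale has at most 24-30.
- **Trial** (Implementing the cRCT). At least 16 new classes take part, and "a minimum of 400 children will be involved in this small-scale cRCT". All classes complete the scale one week before the intervention. The analyses named for these data are mixed and multilevel models and descriptive statistics. The Abstract makes the scale scores the primary end point.

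**The concern.** A confirmatory factor analysis carries weight when it could have failed. If the items were kept because they behaved well in a given data set, a model of those items fitted to the same data has been helped to fit. Part of what made each item look good was chance, or something particular to those 10 classes, and that part will not recur in other children. The second administration is a new occasion but not a new sample, and it is the occasion on which the selection is made.

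The protocol gives scale validation equal standing with the intervention in its principal objective. The Conclusions present the scale as the first of its kind, for translation and international use. Evidence of structural validity from the children who shaped the scale is thin support for that claim.

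**Working it through.** **1. Which children enter which analysis**

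| Data | Children | Use stated |
|---|---|---|
| Administration 1 | about 250, 10 classes | EFA, CFA, items may be added or removed |
| Administration 2 | the same 250 | item reduction, EFA, CFA |
| Administration 3 | subsets of the same 250 | responsiveness; test-retest |
| cRCT baseline | at least 400, at least 16 new classes | effect models and description only |

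New children in any stated confirmatory analysis of the final items: 0. If the data set used for item reduction means both administrations pooled, the count is still 0.

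The head counts agree with each other at 25 per class: 10 × 25 = 250 and 16 × 25 = 400. The Abstract gives 300 children and at least 20 classes instead. That mismatch does not affect this point.

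**2. How heavy the selection is**

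24/6 = 4 and 30/6 = 5, so about 4 or 5 of 10 items survive per dimension. Respondents per item at the first administration: 250/60 = 4.2.

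**3. Illustrative optimism in reliability**

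Optimism is Cronbach alpha in the selection sample (n = 250) minus alpha of the same items in new children. The article gives no loadings, so they are assumed. The selection rule, highest item-rest correlation, is also assumed.

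| Items kept of 10 | Assumed loadings | Optimism in subscale alpha |
|---|---|---|
| 4 | 0.2-0.6 | 0.029 |
| 4 | 0.3-0.5 | 0.058 |
| 4 | 0.1-0.5 | 0.054 |
| 4 | 0.3-0.7 | about 0.015 |
| 4 | 0.4-0.8 | about 0.008 |
| 5 | 0.3-0.6 | 0.66 − 0.63 = 0.03 |
| 5 | 0.2-0.5 | 0.53 − 0.48 = 0.05 |
| 5 | all 0.4 | 0.56 − 0.49 = 0.07 |

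The last row is a limiting case: the items are equally good, so selection acts on chance alone. For a total over all dimensions the optimism is smaller: 0.01-0.03 at the weak loadings and 0.003 at 0.4-0.8. I re-ran these settings and obtained the same picture. None of the runs includes clustering by class or a confirmatory fit index.

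**4. Where an independent test could come from**

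- *Splitting the 250:* 125/30 = 4.2 to 125/24 = 5.2 respondents per item, below the article's own rule of 10. Selecting on only 125 also raises the optimism, to 0.059, 0.095 and 0.096 in the first three settings of the table.
- *cRCT baseline:* 400/30 = 13.3 to 400/24 = 16.7 respondents per item, which meets that rule.

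**5. Limits of the cRCT baseline**

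A 24-item, six-factor model has 24 loadings + 24 residual variances + 15 factor covariances = 63 parameters, against 16 classes. A cluster-robust covariance matrix has rank of at most about 16, so a robust overall fit test would be unreliable. As a rough guide, take intraclass correlations of 0.01-0.10 (assumed) and 25 per class. The design effect 1 + 24 × ICC is then 1.24-3.40, and 400 children carry the information on a mean of about 323 down to 118.

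**The case against.** **The factors are not chosen by the data.** The six dimensions come from the Child-Focused MHL model, and items are assigned to them before any child answers. A reader might infer that the confirmatory analysis is wholly circular. The text does not support that. At the first administration it tests a prior model, and changes made then are examined on fresh responses at the second. This objection stands, and it confines the problem mainly to the choice of items within dimensions.

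**Silence is not proof.** The figure showing the data flow is not available and the analysis plan is not at hand, so a hold-out cannot be excluded. That is fair. But the text does state which data serve item reduction and both factor analyses, and what the result is to be called. That is a stated method rather than an omitted detail.

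**The size may be negligible.** With strong loadings the optimism in alpha is close to zero. Alpha is not named in the article, and it is not a measure of structural fit. This also stands, so the size has to be given as a range that reaches almost to zero.

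**The trial is unaffected.** A reader might infer that the treatment effect or the type I error is compromised. Neither follows. The cRCT scores new children in both arms with the same instrument, and no stated sample size calculation uses the reliability.

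**Moving all confirmatory work to the trial would be worse.** The primary end point would then enter the cRCT with no structural check at all. This is correct, and the planned analyses should stay.

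**Conclusion.** The point holds for the items within each dimension. On the plan as written, structural validity of the final scale is judged on responses from the children whose data selected it, and no later analysis described corrects this. Expect some optimism in fit and reliability. For subscale alpha it is illustratively about 0.03-0.06 with weak loadings (0.07 in the limiting case of equal ones) and about 0.01 or less with strong ones. These sizes rest on assumed loadings and a simplified selection rule. Optimism in confirmatory fit is expected by the same mechanism but has not been quantified.

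The consequence is for the scale-validation objective. The change is worth making because children who could supply the independent test are already due to complete the scale.

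**What to change.** 1. Keep the planned exploratory, confirmatory and item-reduction analyses on the 250 children, and label them as development-sample results.
2. Freeze the item list and the six-factor model before the cRCT begins.
3. Prespecify one replication confirmatory factor analysis and one reliability analysis on the cRCT baseline, pooled regardless of arm and using only the administration before the intervention.
4. Allow for clustering by class, with caution because classes are few. A sensitivity analysis on within-class data (responses centred on the class mean) avoids leaning on robust inference from 16 clusters.
5. Report the replication as the main evidence of structural validity. Leave the prespecified primary end point score unchanged whatever the fit. The article does not say whether this is a total or a set of dimension scores, so the wording should refer to whichever is prespecified.

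The cost is a few sentences in the protocol or analysis plan and slightly more analysis, with no further data collection. The drawback is timing: the replication arrives only after the form is fixed, so it can qualify the claim for the scale but cannot improve the version used in the trial.

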### Objectives, Hypotheses, and Scope

The principal objective of the CHILD-MHL project is 2-fold. It aims to (1) implement an intervention and evaluate its effectiveness concerning children’s MHL and (2) develop and validate a scale measuring children’s MHL.

The CHILD-MHL intervention and the CHILD-MHL scale are the core outputs of the project. They are built in parallel, and they are strongly associated with one another. The effectiveness of the intervention cannot be tested without a scale whose responsiveness can be proved only by an intervention.

The specific objectives are to (1) enhance the effectiveness of the CHILD-MHL intervention using different features—cocreation and design thinking, whole-school approach, theory-based approach, and multitools; (2) outline the CHILD-MHL scale—defining and testing items, administering the scales to a large sample of children, and conducting psychometric analyses for the final validation; and (3) evaluate the effectiveness of the CHILD-MHL intervention using different techniques and methods—performing a viability evaluation, performing a cluster RCT (cRCT), and using mixed methods.

The first hypothesis is that a cocreated, whole-school, theory-based, and multitool intervention makes the intervention itself effective. The second hypothesis is that, to be robust, a scale should be developed through different steps, from an inventory of items (the largest number as possible), their test among the target audience, and the administration in a large sample. The third hypothesis is that strong evidence of the effectiveness of an intervention is provided by the combination of several types of study and the collection of as much data as possible (quantitative and qualitative).

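### Responsiveness of the CHILD-MHL scale is inferred from any score change in the intervention classes alone, so drift over 3 months could pass for sensitivity to the intervention

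*Protocol article*

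**What the plan says.** All the relevant text is in the protocol article, under Validation of the CHILD-MHL Scale.

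- **First to second administration.** About 250 children in 10 classes answer the scale, and half of those classes belong to the viability evaluation. "After 3 months, the questionnaire with the scale, which might have been modified, will be readministered for the second time", to all 10 classes, in the week before the pilot intervention begins.
- **Intervention classes.** "Children from the 5 classes of the viability evaluation intervention will complete the questionnaire for the third time after a 3-month interval". Their role is explicit: "Data collected from these classes will be used to assess the sensitivity to change or responsiveness of the scale".
- **Criterion.** "If the score changes after the intervention, it indicates that the scale can measure the effect of the intervention". The article then describes the items as ones that interventions can influence.
- **Untreated classes.** "children not receiving the intervention will answer the questionnaire for the third time after a month". Their use is also explicit: "Data will be used to assess the test-retest reliability, determining whether answers remain consistent between administrations".

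The article describes no comparison of change between the two sets of classes and states no expected direction or size of change. The Abstract makes the scale score the primary end point of the later cluster trial.

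**The concern.** By the third administration the pilot children have met the scale twice before, are 3 months older and have had 3 more months of school. The article itself, under The Population Under Study, describes ages 9 to 11 as a time of cognitive, emotional and social development, so some change without any intervention is plausible. A one-group criterion attributes all of it to the intervention. Read literally, even a fall in score would satisfy it.

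At stake is the choice of endpoint. Responsiveness is the property that tells the team whether the scale can register what the intervention does. If drift is mistaken for it, an insensitive scale may be adopted. A null cluster trial would then leave open whether the intervention failed or the scale could not show its effect.

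**Working it through.** The article gives no test, significance level, effect size or sample size for responsiveness, so there is no stated figure to reproduce. The calculation below asks how often drift alone would look like responsiveness.

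**Inputs from the article**
- Children in the intervention classes: 10 classes and about 250 children give about 25 per class, so 5 classes hold 125. The Viability Evaluation section gives about 130, in 4 classes rather than 5. Both totals are used; the difference in class count does not affect the point.
- Pre-post interval: 3 months, from the second to the third administration.

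**Assumptions not in the article**
- Zero intervention effect.
- Drift d of 0.1, 0.2 or 0.3 SD over 3 months.
- Pre-post correlation r = 0.6.
- A two-sided 5% test of mean change.
- For clustering, a design effect on change of 1 + 25 × 0.03 = 1.75, from an intraclass correlation of 0.03 and classes of about 26.

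**Formulas (SD units)**
- SE = √(2(1 − r)/n), multiplied by √1.75 = 1.323 with clustering.
- P(significant) ≈ Φ(d/SE − 1.96).

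**Standard errors**
- n = 125: √(0.8/125) = 0.080, or 0.106 with clustering.
- n = 130: √(0.8/130) = 0.078, or 0.104 with clustering.

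**Drift of 0.2 SD**
- n = 125, no clustering: Φ(2.50 − 1.96) = Φ(0.54) = 0.71.
- n = 130, no clustering: Φ(2.55 − 1.96) = Φ(0.59) = 0.72.
- n = 125, clustered: Φ(1.89 − 1.96) = Φ(−0.07) = 0.47.
- n = 130, clustered: Φ(1.93 − 1.96) = Φ(−0.03) = 0.49.

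| Drift | Ignoring clustering | Design effect 1.75 |
|---|---|---|
| 0.1 SD | 24-25% | 16% |
| 0.2 SD | 71-72% | 47-49% |
| 0.3 SD | 96-97% | 81-82% |

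**Sensitivity to r and to the test.** With n = 125 and no clustering, 0.2 SD of drift gives 61% at r = 0.5 and 94% at r = 0.8. A simulated t test on 5 class means (r = 0.7, 25 children per class) gives 60% with an intraclass correlation of change of 0, and 32% with 0.05.

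**Would the 1-month data serve as a control?** Not fully. If drift is linear in time, a 1-month reference removes one third of it. Of 0.2 SD, 0.2 × 2/3 = 0.13 SD remains.

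**With a concurrent 3-month comparison.** A class-level test of the difference in change, 5 classes against 5, was simulated with r = 0.7 and intraclass correlation 0 or 0.05. With no intervention effect, significance appears in 4.7% to 5.4% of runs for any drift from 0 to 0.3 SD. A true effect of 0.5 SD is detected with probability 0.995 or 0.86, and one of 0.3 SD with probability 0.76 or 0.43, at intraclass correlation 0 or 0.05 respectively.

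**The case against.** The strongest reply is that the cluster trial does not inherit this weakness. Under Implementing the cRCT, it uses new classes, allocated at random within matched pairs against a waiting list, with the scale given at the same times in all classes. Shared drift cancels in that contrast. This stands, and it limits the harm to the choice and interpretation of the endpoint.

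Three stronger readings are tempting, and the article does not support them.

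- **Circularity.** A reader might infer this from the Objectives section, which speaks of "a scale whose responsiveness can be proved only by an intervention". But needing an intervention to show responsiveness is not circular in itself, and a drift artefact in uncontrolled pilot classes cannot create a difference between randomised arms in other children.
- **Items tuned to noise.** A reader might infer that items are kept because they moved in the pilot. The article places item reduction at the second administration, before the intervention, using Classical Test Theory and Item Response Theory. Nothing says items are selected on post-intervention change.
- **A wrong 1-month interval.** It is assigned to test-retest reliability and suits that purpose. Moving it to 3 months would not help unless the criterion also became comparative.

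It can also be said that the criterion sentence sets no formal threshold or gate to the trial, that the article commits to COSMIN, and that details may sit in a fuller document. That is fair as to thresholds. It does not answer the point, because the article itself fixes the measurement schedule and the one-group inference, and no later analysis plan can supply a 3-month measurement that was never taken.

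Finally, some data on drift will exist: the untreated first-to-second interval and the 1-month retest. This is true, but the article assigns neither to this use, and the scale may change between the first two administrations.

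**Conclusion.** The point holds as a fault in how one measurement property is assessed. The criterion uses one group, and the untreated classes have no concurrent 3-month measurement, so the planned data cannot separate intervention effect from drift.

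The size depends on assumptions. With no intervention effect, 125 to 130 children and r = 0.6, the chance of a misleading significant change runs from 16-25% at 0.1 SD of drift to 81-97% at 0.3 SD, where each range spans the clustered and unclustered calculations. The spread mainly reflects the drift chosen, and the article offers no basis for picking a value.

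The consequence is a possibly insensitive primary endpoint and a null trial that is hard to interpret. A reader might go further and infer that the trial could falsely prove efficacy; the randomised waiting-list design does not support that. This is a worthwhile, inexpensive correction to the validation stage, not a flaw in the randomised comparison.

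**What to change.** 1. **Change the criterion.** Define responsiveness as the class-adjusted difference in 3-month change between intervention and non-intervention classes, with the direction stated in advance.
2. **Add the data.** Give the scale once more, at 3 months, in the roughly 5 untreated classes, and keep the 1-month administration for test-retest reliability. The cost is one supervised tablet session per class, in classes already enrolled. Five classes against five will be imprecise for smaller effects, as the detection probabilities above show, so report the estimate with its interval and not only a test result.
3. **At minimum, with no new data.** Compare the intervention-period change with the untreated first-to-second administration change, on the items common to both. State that this reference is rough, because the scale may have been modified and the period is earlier.
4. **If neither is done.** Do not present the pilot pre-post change as evidence of responsiveness. Assess responsiveness from the randomised contrast in the cluster trial, and accept that this comes only after the endpoint has been chosen.

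The decision should be made before the second administration, while the untreated classes can still be scheduled alongside the pilot classes.
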